---

## 1. Purpose

This study will investigate the association between a set of single nucleotide polymorphisms (SNPs) and atrial fibrillation in patients at high risk of developing atrial fibrillation. The SNPs investigated will have been previously shown to be associated with the atrial fibrillation.

## 2. Background

Atrial fibrillation is the most commonly encountered arrhythmia [1, 2] and when documented is predicted to be responsible for approximately 25% of strokes [3-5]. However, 25% of persons who suffer an ischemic stroke have no cause identified [3, 4, 6, 7]. In reality, many of these strokes are likely to be accounted for by atrial fibrillation [7, 8]. With 30 - 40% of ischemic strokes being classified as cryptogenic [9-14] it is imperative that greater efforts be taken to diagnose and treat those strokes that are due to treatable conditions such as atrial fibrillation. Because subclinical atrial fibrillation goes unrecognized by the patient it could be said to pose the greatest risk. Figures vary as to the prevalence of subclinical atrial fibrillation but implanted cardiac device studies in those without previously documented atrial fibrillation suggest it is indeed common [15, 16] and carries an increased risk of stroke or systemic embolism [3]. With recent studies highlighting the potential deficiencies of aspirin treatment in atrial fibrillation [17] it has become critical that we accurately identify all subgroups of atrial fibrillation and initiate appropriate treatment to reduce the risk of stroke.

Although atrial fibrillation can follow a familial pattern [18] more defined screening strategies need to be identified to target non-familial atrial fibrillation. To date, several genome-wide association studies (GWAS) have identified and replicated a panel of SNPs that occur more commonly in persons with atrial fibrillation. The SNPs with the most predictive utility are rs2200733 and rs10033464 on chromosome 4q25 [1, 19-27], rs2106261 on chromosome 16q22 [20, 21], and rs13376333 on chromosome 1q21 [22]. Several other SNPs have also had been associated with atrial fibrillation at a GWAS level ( $P < 5 \times 10^{-8}$ ) [47].

Of those SNPs on chromosome 4q25, rs2200733 was first reported to have an odds ratio of 1.84 for atrial fibrillation (1.51 - 2.23,  $P = 9.8 \times 10^{-10}$ ) and rs10033464 an odds ratio of 1.30 (1.00 -

1.69,  $P = 0.052$ ) in the United States population [1], and when combined with other populations of European ancestry the association of rs10033464 moved well beyond the threshold of genome wide significance ( $OR = 1.39$ ,  $P = 6.9 \times 10^{-11}$ ) [1]. With multiplicative models, the combined population attributable-risk (PAR) of both variants is approximate 20% in European ancestral populations [1]. It is estimated that approximately 35% of persons of European heritage have at least one of the variants [1]. Increasing copy number also confers a greater risk of atrial fibrillation [1]. Interestingly, the age at diagnosis of atrial fibrillation occurs between 1.10 and 2.28 ( $P = 1.29 \times 10^{-6}$ ) years earlier in those who carry the risk variants. Although both variants reside in a linkage disequilibrium (LD) block that do not contain any genes, the closest gene, PITX2, is located in an upstream LD block and is important in myocardial development because it directs asymmetric atrial morphogenesis [1, 28]. Mouse knockout models have shown it to suppress pathways for sinoatrial node formation [29, 30].

SNP rs2106261 on chromosome 16q22 has an odds ratio of 1.44 for atrial fibrillation ( $P = 1.6 \times 10^{-11}$ ) in persons of European descent [20], and occurs in approximately 20% of that population [19]. This SNP is located around zinc finger homeobox 3 (ZFHX3) gene [19], which encodes a transcription factor that acts as a regulator of alpha-fetoprotein expression [19, 31]. Its role in cardiac or pulmonary tissue physiology remains unclear.

A recent GWAS focusing on lone atrial fibrillation found that the SNP rs13376333 on chromosome 1q21 was associated with lone atrial fibrillation in persons of European ancestry. Carriers of the minor allele of this SNP were at 50% increased risk for developing lone atrial fibrillation:  $OR$ , 1.52 (95%  $CI$ , 1.40 - 1.64;  $P = 1.83 \times 10^{-21}$ ) [19, 22]. This SNP is located between the first and second exons of *KCNN3* [19], a calcium-activated, small conductance potassium channel, and its involvement in rabbit models of pulmonary venous ectopy provide a plausible biological pathway for the development of atrial fibrillation [32]. Furthermore, six additional variants have recently been discovered by Ellinor et al. and although the reported odds ratios were modest, these associations achieved genome-wide significance [47].

### 3. Hypothesis

Our primary hypothesis is that a risk score comprised of approximately 10 SNPs that are associated with atrial fibrillation at the GWAS level is associated with the development of atrial fibrillation among previously undiagnosed patients at high risk for atrial fibrillation. A current example of these SNPs is shown in Table 1. As a secondary hypothesis, we will test the association between atrial fibrillation diagnosed in this study with a subset of SNPs reported to be associated with atrial fibrillation and with fine-mapping SNPs. We will also test the association between atrial fibrillation of less than and greater than 30 seconds and a panel of approximately 10 SNPs.

We propose to perform targeted genotyping of patients at high risk for atrial fibrillation who are referred for ambulatory cardiac rhythm monitoring. To potentially increase our diagnostic yield, cardiac rhythm monitoring may be performed for up to two weeks using a prolonged-duration ambulatory ECG recording device such as the iRhythm Zio® Patch or the Sorin Spider Flash-t™ loop recorder.

**Table 1.**

| rs#        | Locus | Gene    | OR source    | OR (95% CI)      | AF    |
|------------|-------|---------|--------------|------------------|-------|
| rs2200733  | 4q25  | PITX2   | [1] and [25] | 1.76 (1.49-2.07) | 0.115 |
| rs10033464 | 4q25  | PITX2   | [1] and [25] | 1.32 (1.23-1.42) | 0.097 |
| rs2106261  | 16q22 | ZFHX3   | [47]         | 1.24 (1.17-1.30) | 0.181 |
| rs13376333 | 1q21  | KCNN3   | [47]         | 1.18 (1.13-1.23) | 0.336 |
| rs3903239  | 1q24  | PRRX1   | [47]         | 1.14 (1.10-1.17) | 0.448 |
| rs3807989  | 7q31  | CAV1    | [47]         | 0.90 (0.87-0.92) | 0.42  |
| rs10821415 | 9q22  | C9orf3  | [47]         | 1.11 (1.08-1.15) | 0.397 |
| rs10824026 | 10q22 | SYNPO2L | [47]         | 0.87 (0.83-0.91) | 0.165 |
| rs1152591  | 14q23 | SYNE2   | [47]         | 1.13 (1.09-1.17) | 0.487 |
| rs7164883  | 15q24 | HCN4    | [47]         | 1.19 (1.14-1.24) | 0.168 |

### 4. Study Design

This will be a multi-center, bi-national prospective study involving patients who are at high risk for atrial fibrillation and are referred for ambulatory cardiac rhythm monitoring or have a first diagnosis of atrial fibrillation by electrocardiogram (ECG) on the day of their enrollment. .

Patients defined, as high risk for atrial fibrillation will be persons with:

1. No prior history of atrial fibrillation and/or atrial flutter (AFIB/AF) - with symptoms of high clinical suspicion for AFIB/AF prompting referral for ambulatory cardiac rhythm monitoring to evaluate for potential AFIB/AF, and
2. Any of the following features: ischemic stroke or TIA with no defined etiology (In prior 6 months) [3, 4, 6, 7], hypertension [33], increased body mass index (BMI >30kg/m^2) [33], heart failure [33], clinically significant murmur [33], prolonged PR interval on resting ECG (>200msec) [33], chronic kidney disease [34], hypertrophic cardiomyopathy [35], congenital heart disease [36], chronic obstructive pulmonary disease [37, 38], sleep apnea [39-41], thyroid disease [42, 43], family history of atrial fibrillation [44], diabetes [45] or excess alcohol consumption (Male > 14 drinks/week, Female >7 drinks/week)[46].

Patients will be 40 years or older and capable of providing informed consent, providing a blood sample and wearing a Zio® Patch for up to 14 days or a Sorin SpiderFlash-t™ for up to 21 days. Each patient will be identified by a unique study number (e.g. 001) and their initials. (Patient initials will not be listed on the sample tubes.) Patients who receive the Zio® Patch or the SpiderFlash-t™ will be registered on their respective websites by their study ID.

Atrial fibrillation or flutter is defined using standard electrographic criteria and a minimum event duration of 5 seconds [3, 6].

Physicians and/or medical centers that routinely investigate patients at high risk for atrial fibrillation will be selected for participation. The care team will identify eligible patients for this study at the time of their medical assessment. Additionally, patients may also be identified when they present as ‘walk ins’ to the cardiac investigations laboratory. All potential patients will be provided with an informed consent form. If a patient is then agreeable to inclusion in the study a coordinator will then take the patient to a private room, inform them of the study details, and provide them with adequate time to read the informed consent form (ICF). The study coordinator

will review the ICF with the patient and answer all of their questions. The patient will sign the ICF and the coordinator and the patient will proceed to the cardiac rhythm monitoring lab and/or the laboratory. Patients who presented with symptoms and a diagnosis of atrial fibrillation was confirmed at the time of the visit by an (ECG) will not be fitted with a monitoring device but provide blood for genetic testing and future research. Patients who otherwise meet inclusion/exclusion criteria will be fitted by the technician with a Zio® Patch or SpiderFlash-t™ loop recorder. All patients will provide a blood sample (in a 4 ml EDTA tube) for genotyping and a serum sample (in 2 x 10ml serum separating tubes) for future research. (These patients may also be fitted with a traditional Holter monitor).

### **iRhythm Technologies Zio® Patch**

If the patient is fitted with a Zio® Patch they will be provided the Patient Instructions and Diary booklet (Appendix 1) with instructions for recording any symptoms experienced while wearing the patch. They will also receive the Zio® Patch Return Box - a pre-paid box for return of the Zio® Patch to iRhythm Technologies. The patient will continue to wear the Zio® Patch for up to 14 days. Upon completion, the patient will remove the device and return it to the device manufacturer by prepaid box, for data processing and generation of a report of the findings.

The results of Zio® Patch monitoring will be analyzed by the staff of iRhythm Technologies, Inc. The data from the Zio® Patch will not be relied upon to make timely clinical diagnoses, but rather the information obtained will be used to help us more accurately assess our approach to treating these patients.

Upon review of the report, an iRhythm representative will notify the principal investigator by phone and follow up e-mail if there are any significant findings. (See Appendix 2 for Zio® Patch Notification Criteria.)

The site investigators will be notified by e-mail when there is a new report available on the website for his review. (See Appendix 3 for Zio® Patch Sample Report.) The site investigators will log-on with a unique ID, review the report, add comments, and sign off on the report.

**Sorin SpiderFlash-t™ Loop Recorder**

Patients enrolled in British Columbia will be outfitted with a Sorin SpiderFlash-t™ Loop Recorder, an automatic and patient-activated long-term cardiac loop recorder. In addition to being patient activated, the Spider Flash is automatically programmed to activate recording if it senses atrial fibrillation. The recorder is water- and shock-resistant, and is supplied with a disposable water resistant plastic holster that hangs around the patient's neck. A patient diary with ECG connection instructions is provided to assist the patient with replacement of the recording electrodes to allow for bathing and skin care during the time the patient is wearing the recorder.

Events that are considered possible occurrences of atrial fibrillation will be adjudicated by a physician with expertise in cardiac rhythm interpretation. Primary end point events will be instances of atrial fibrillation/flutter.

**5. Sample Storage and Analysis**

A blood sample (in a 4 ml EDTA tube) for genotyping and a serum sample (in two 10ml red top tubes) for future research will be obtained from each patient.

Blood samples will be delivered to the site's laboratory or storage area. The serum sample will be centrifuged and the serum stored in a -80° freezer. (If no -80° freezer is available, sites may store the samples in a -20° freezer, as long as it is not a "frost-free" freezer.) The blood sample will be stored in a -80° or a -20° "frost free" freezer. The blood and serum samples will be stored sent via overnight courier to Celera, Alameda, approximately one time per month.

Celera will perform Genotyping on subject blood samples and DNA will be stored at Celera for future research. Serum samples will be stored at Quest Diagnostics for use in future research.

Sites will receive a "Laboratory Reference Manual" for instructions on sample collection and storage.

**Future research**

By signing the informed consent and enrolling in the study, patients are consenting to the genotyping of their blood sample for the purposes of exploring the association between the identified SNPs and the risk of developing atrial fibrillation.

Patients will be given the option to opt out of future research by placing a check mark before the following statement in the informed consent:

☐ Check here if you **do not** want your sample used for **future cardiovascular disease research.**

If patients agree to future research, samples and subject information will be kept for up to 20 years. In 2033, the code that links the sample to the subject's traditional identifying information will be destroyed.

## 6. Statistical Considerations

SNP effect sizes and frequencies were determined from the literature and the International HapMap Project database as indicated in Table 1. Expected occurrences of atrial fibrillation in the two groups were calculated using reference to previous studies as outlined above [7, 8, 33]. We expect 80 atrial fibrillation events in a 1000 high-risk patients [48, 49]. Using these event rates and an alpha error of 5%, the power to detect an association between a 10-SNPs risk score and atrial fibrillation is >90%. The power to detect association between a 4-SNP risk score and atrial fibrillation is >80%.

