## **13. Estimated Duration of Study**

The study will be conducted at multiple participating research sites in order to meet the study enrollment goals in a timely manner. If the endpoint of 80 atrial fibrillation/flutter events have not been met at the end of 2 years, the timeline and enrollment may be extended until 80

endpoint (atrial fibrillation/flutter) events are recorded. If 80 endpoint events have occurred before 650 patients are enrolled, enrollment may be terminated before 650 patients are enrolled.

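### Sections 6 and 13 give unreconciled study sizes (1000 and 650 patients), and the 80-event target on which the stated power rests is not binding

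*Protocol*

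**What the plan says.** Protocol Section 6 (Statistical Considerations) sets the size: "We expect 80 atrial fibrillation events in a 1000 high-risk patients [48, 49"]. It then names the basis of the power calculation: "Using these event rates and an alpha error of 5"%. For the larger score it claims: "the power to detect an association between a 10-SNPs risk score and atrial fibrillation is >90"%. For the smaller score: "The power to detect association between a 4-SNP risk score and atrial fibrillation is >80"%. The inputs are given by reference: "SNP effect sizes and frequencies were determined from the literature and the International HapMap Project database as indicated in Table 1".

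Protocol Section 13 (Estimated Duration of Study) repeats the target of 80 AF/flutter events. If it has not been met after 2 years, the timeline and enrolment are allowed, not required, to run on until it is. The section then adds: "If 80 endpoint events have occurred before 650 patients are enrolled, enrollment may be terminated before 650 patients are enrolled". The figure of 1000 does not appear in Section 13, and 650 does not appear in Section 6.

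Two other places bear on the point. Section 17 (Subject Withdrawal) has withdrawn or ineligible subjects replaced until the endpoint is met. Sections 4 and 7 admit patients whose AF is first diagnosed by ECG on the day of enrolment. These patients are not fitted with a monitor.

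**The concern.** The two sections agree on 80 events but not on how many patients it takes to get them. Section 6 implies 1000. Section 13 treats 650 as the natural benchmark: a clause on stopping before 650 has a purpose only if about 650 patients are expected. No sentence links the two numbers or gives an event rate that would.

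This matters because the >90% and >80% figures belong to 80 events, and the protocol does not oblige the sponsor to reach 80. A trial that closed at 2 years with about 650 patients and the Section 6 event rate would have followed the protocol and still fallen short of its stated power. The data safety and monitoring board is also asked in Section 10 to judge cumulative enrolment, event rates and expected trial length. For that it needs one planned N and one rate.

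**Working it through.** **Inputs.** Event rate 80/1000 = 8% and alpha 5% (Section 6; sidedness not stated, so two-sided is the base and one-sided is also shown). Odds ratios and allele frequencies for ten SNPs come from Table 1, for example "1.76 (1.49-2.07) | 0.115" for rs2200733. Patient benchmark 650 (Section 13). The 4-SNP score is taken as the first four rows of Table 1. This is an assumption: they are the four that Section 2 singles out, in a sentence beginning "The SNPs with the most predictive utility are rs2200733 and rs10033464 on chromosome 4q25".

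**Step 1: consistency of the sizes.**
- Patients needed for 80 events at 8%: 80 / 0.08 = 1000.
- Expected events in 650 patients at 8%: 650 × 0.08 = 52.
- Yield needed for 80 events in 650: 80 / 650 = 12.3%.
- Chance of at least 80 events in 650 patients at 8% (exact binomial): about 0.0001.

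On Section 6's rate, then, the early-stopping clause of Section 13 would almost never come into play.

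**Step 2: variance of the score.** For a log-OR-weighted score with independent loci in Hardy-Weinberg proportions, V = Σ (ln OR)² × 2f(1 − f). For rs2200733, (ln 1.76)² × 2 × 0.115 × 0.885 = 0.065. Summing gives V = 0.1449 for ten SNPs and 0.1045 for the first four.

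**Step 3: power formula.** Power = Φ( √[N p (1 − p) V] − z ), with z = 1.96 two-sided. This is a small-effect approximation. It was checked by simulating genotypes and applying a score test (6000 runs per scenario).

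**Step 4: reproduce the stated figures at 80/1000.** N p (1 − p) = 1000 × 0.08 × 0.92 = 73.6.
- 10-SNP: √(73.6 × 0.1449) = 3.27, giving 90.4% (simulation 93.8%).
- 4-SNP: √(73.6 × 0.1045) = 2.77, giving 79.2% (simulation 85.7%).

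The stated >90% and >80% are reproduced, the second within the spread of the two methods. Section 6 is therefore sound on its own terms. An unweighted 10-SNP allele count gives only 79.1% (simulation 82.0%) at this size, so the stated figure implies weighting.

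**Step 5: the same model at the other sizes.** At 52/650, N p (1 − p) = 650 × 0.08 × 0.92 = 47.84. At 80/650 it is 80 × (1 − 80/650) = 70.15.

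| Events / patients | Test | 10-SNP: formula / simulation | 4-SNP: formula / simulation |
|---|---|---|---|
| 80 / 1000 | two-sided | 90.4% / 93.8% | 79.2% / 85.7% |
| 80 / 650 | two-sided | 89.0% / 91.0% | 77.3% / 83.3% |
| 52 / 650 | two-sided | 74.9% / 79.1% | 60.9% / 68.3% |
| 52 / 650 | one-sided | 83.8% / 86.3% | 72.3% / 77.3% |

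A further simulation of 52/650 put the 10-SNP figure at about 80%, hence the range of 75-80%. With 52 events both claims are missed, one-sided or two-sided. With 80 events in 650 patients the loss against 80/1000 is about 1 to 3 percentage points.

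**The case against.** The best defence is that the study is driven by events. Sections 6 and 13 share the target of 80, Section 13 provides for extension until it is reached, and Section 17 replaces subjects until then. The number 650 appears only in a sentence that presupposes 80 events have already occurred, and in that case power is close to what is stated. A reader might infer that 650 is a cap, or that the plan as written misses its power. The protocol supports neither: nothing makes 650 a maximum, and the shortfall arises only if the extension is not used. The same permission would equally allow closure at 2 years at some other size. Nor is there an arithmetic error within Section 6.

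The 8% may also be too low for the population now admitted. If patients with AF on the enrolment-day ECG count as events, the yield will exceed that from monitoring alone, and 650 might reflect this. But the protocol gives neither their share nor that explanation, and if it is the reason, the rate in Section 6 is out of date.

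What stands after this: 1000 and 650 are never reconciled, the 12.3% yield is nowhere stated, and the target that secures the power is optional.

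**Conclusion.** The point holds in conditional form. The inconsistency between 1000 and 650 is on the face of the protocol and depends on no modelling. The loss of power does depend on a condition: enrolment closes at 2 years near 650 patients, the yield is 8%, and the permitted extension is not used. Two-sided power is then about 75-80% for the 10-SNP score and 61-68% for the 4-SNP score, some 10 to 15 and 12 to 19 points below the stated thresholds of 90% and 80%.

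The size of the shortfall rests on a log-OR-weighted score, Table 1 odds ratios and frequencies holding in this population, independent loci (two of the ten SNPs lie at 4q25), and the choice of the four SNPs. The sponsor would need to confirm these, so the figures show the scale of the problem and are not replacement text for the protocol.

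**What to change.** 1. State one planned number of patients and one expected event rate, identically in Sections 6 and 13.
2. Say whether AF diagnosed by ECG on the day of enrolment counts towards the 80 events, and what yield is assumed with those patients included or excluded.
3. Choose one of two courses. Either make the target binding, so that Section 13 says enrolment will be extended until 80 events are recorded (about 1000 patients at 8%). Or keep the extension optional and have the sponsor restate power for the size at which enrolment may close, giving the score weighting, the sidedness and the four SNPs used.
4. Justify the 650, for instance by stating the yield behind it, or delete it.

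The cost is a wording change in two sections. A binding target may mean a longer study and more patients than 650. Keeping it optional means stating a lower power for early closure.

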## 7. Inclusion and Exclusion Criteria

Inclusion Criteria:

- **(1) Symptoms of high clinical suspicion for atrial fibrillation prompting referral for ambulatory cardiac rhythm monitoring for potential atrial fibrillation OR (2) initial presentation and diagnosis of atrial fibrillation with in-office or in patient ECG on the day of enrollment.**

**AND**

- At high risk for atrial fibrillation, defined as any one of the following: ischemic stroke or TIA with no defined etiology (in prior 6 months) [3, 4, 6, 7], hypertension [33], increased body mass index ( $\text{BMI} > 30 \text{ kg/m}^2$ ) [33], heart failure [33], clinically significant murmur [33], prolonged PR interval on resting ECG [33], chronic kidney disease [34], hypertrophic cardiomyopathy [35], congenital heart disease [36], chronic obstructive pulmonary disease [37, 38], sleep apnea [39-41], thyroid disease [42, 43], family history of atrial fibrillation [44], diabetes [45] or excess alcohol consumption (Male  $> 14$  drinks/week, Female  $> 7$  drinks/week)[46].
- Age 40 years or older
- Capable of providing informed consent
- Capable of wearing a Zio Patch for up to 14 days or Sorin SpiderFlash-t™ loop recorder for up to 21 days.
- Capable of providing a blood sample

